### Interim analyses {21b}

The behavioral interventions are considered to be minimal risk, and the data collection procedures impose only modest burden on participants. Accordingly, no interim analyses are planned, as there is not a compelling reason or rationale for early termination of the trial, even if any differences in the outcomes begin to emerge earlier than expected, and analyses involving preliminary data could lead to spurious conclusions that may impair the credibility of the findings. However, if the Data and Safety Monitor/Medical Safety Officer (DSM/MSO) requests interim outcomes analyses based on new evidence from the trial or other researchers such that the risks of study treatments are substantially greater than anticipated, the interim analyses will be performed. Similarly, the DSM/MSO may terminate the trial if trial safety measure data suggest safety issues or if recruitment and retention or data quality are so impaired that the study aims could not be met.

### Methods for additional analyses (e.g., subgroup analyses) {20b}

ICIQ-Nqol scores and PSQI Global scores will be modeled similarly with (G)LMMs in their original scale or transformed scale as appropriate, with similar fixed effects and random effects as proposed in Aims 1 and 2. If the distributions of the ICIQ-Nqol and PSQI Global scores are skewed and no good transformation is found, the outcomes will be categorized into categories based on quantiles or clinically meaningful values and then modeled with GLMMs using cumulative logit or generalized logit link for multinomial data. Similar fixed and random effects will be included in GLMMs. Due to the exploratory feature, no adjustment will be made for the multiple comparisons, but results will be presented as secondary outcome analyses. Similar secondary analyses as those proposed in Aim 1 will be performed on the secondary outcomes ICIQ-Nqol and PSQI.

### Methods in analysis to handle protocol non-adherence and any statistical methods to handle missing data {20c}

Participant drop-out or loss-to-follow-up levels are expected to be less than 15%, based on observed participant drop-out levels from our multi-center feasibility study. (G)LMM will use all available data in the analyses without dropping participants or including only “completers”, and its estimates are consistent under the assumption of missing at random conditional on observables, a less stringent assumption than the missing completely at random in complete case analysis. The assumption of non-informative participant drop-out will be assessed by comparing baseline characteristics and early post-randomization outcomes of trial dropouts vs. non-dropouts. If participant drop-out rates differ between groups, sensitivity analyses to evaluate the effects of drop-out on estimates of treatment effects will be conducted. Sensitivity analysis will be conducted to assess how much the results from the primary analysis will change 1) if the (G)LMM includes baseline covariates different between dropout and completed participants and 2) if multiple imputation and/or pattern mixture model under plausible informative missingness assumptions to overcome missing data related to participant drop-out is considered. Potential outcome-based causal inference approaches will be used to evaluate the treatment effects while accounting for participants’ nonadherence [65, 66].

### Plans to give access to the full protocol, participant-level data, and statistical code {31c}

The project will result in a deidentified dataset that will contain demographic, subjective and objective (edited and averaged actigraphy data) sleep, and other health-related data of enrolled participants. Materials generated under the project will be disseminated in accordance with the policies at the data coordinating center, and NIH. Data products will be made available without cost to researchers, students, or analysts. To our knowledge, no common data standards exist for multiple key variables examined in this trial, but the deidentified data set will be available in a common format (.csv). User registration and a data use agreement will be required in order to access or download files. As part of the registration process, users must agree to the conditions of use governing access to the public release data, including restrictions against attempting to identify study participants, destruction of the data after analyses are completed, reporting responsibilities, restrictions on redistribution of data to third parties, and proper acknowledgement of the data source. Registered users will receive the data dictionary and user support, as well as information related to errors in the data, future release, workshops, and publication lists. The information provided to users will not be used for commercial purposes and will not be redistributed to third parties. Registered users will be provided access to the full protocol. Statistical code will be made available upon request.

### Composition of the data monitoring committee, its role and reporting structure {21a}

The safety of participants and conduct of the study are further monitored by a DSM/MSO, appointed by and acting in an advisory capacity to the National Institute on Aging (NIA) and the investigator. The DSM/MSO is charged with periodically reviewing the conduct and outcomes of the study and providing feedback to the investigators and the NIA, with particular attention to protecting the safety of the participants. The DSM/MSO is independent of the institution and investigators participating in the study and has no financial, scientific, or other conflict of interest with the trial. The DSM/MSO meets approximately twice yearly during the data collection phase of the trial, unless the NIA Program Official or DSM/MSO requests more frequent meetings.

### Adverse event reporting and harms {22}

New adverse events (AEs), serious adverse events (SAEs), or unanticipated problems (UPs) will be considered reportable any time after the Baseline Visit when participants are randomized until the 4-month follow-up. At each study visit, participants are asked if they have had any significant change in health status since the prior study visit, and if so, a follow-up question about the nature of the change will be asked. Medical or psychiatric conditions that are present at the time that participants are screened are considered to reflect participants’ baseline status and will not be reported as adverse events. However, if a participant’s condition deteriorates at any time during the study, this deterioration will be recorded as an AE even if it is related to a pre-existing condition.

Adverse events are characterized by clinical coordinators at each clinical site in collaboration with the Site PI or other investigators if appropriate. The clinical coordinator in conjunction with the Site PI documents events on standardized AE or SAE forms. The Site PI reviews information about individual AEs collected by coordinators at least twice monthly to guide determinations about the relationship to study interventions, expectedness, and severity. In cases where an AE may be a SAE or represent an Unanticipated Problem, the coordinator will more urgently bring the event to the attention of the Site PI.

The trial follows the VA reporting requirements and timelines for reporting, including ensuring verbal notification of the IRB immediately upon becoming aware of any local research death that is both unanticipated and related to the research, written notification of the IRB within 5 business days after becoming aware of any local SAE that is both unanticipated and related to the research, written notification of the IRB within 5 business days after becoming aware of any serious problem that is both unanticipated and related to the research. SAEs will be reported to the DSM/MSO, and the NIA within time frames specified by these entities, depending on whether events (a) are possibly related to study participation, (b) are unexpected, and/or (c) result in death or are life-threatening:

Any SAEs that are unexpected but potentially related to the intervention will be reported to the DSM/MSO and the NIA within 48 h of the Site PI’s awareness of the event. The team will report other SAEs to NIA Program Officer and to the DSM/MSO in the semi-annual AE summary provided to the DSM/MSO and the NIA, unless otherwise requested. Non-serious AEs that are considered to be UPs, by virtue of being unexpected but possibly related to study participation, will be reported to the DSM/MSO and the NIA within 5 working days of the Principal Investigators’ awareness of the event. The team will report non-serious AEs that are not considered to be UPs to the DSM/MSO and the NIA in the semi-annual AE summary provided to the DSM/MSO and the NIA.

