**Discussion:**

The interdisciplinary trial team has developed a program aimed at improving nocturia symptoms and overall sleep of older adults in an efficient and safe manner. The integrated behavioral program has the potential to address nocturia, which is a challenging symptom because it has many etiologies that cross multiple specialties. Findings will provide rigorous evidence of the efficacy of the integrated behavioral treatment program to reduce nocturia frequency as well as sleep disturbance in older adults.

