Brief telephone check-ins occur up to twice after the participant has completed the integrated program. The goal of these calls is to check in on the participant’s current sleep schedule (time in bed window), stimulus control, Freeze and Squeeze activity, and management of thoughts about sleep and voiding. Activities also include a selective review of prior material based on current complaints.

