#### Healthy aging education control arm

Participants attend visits with the interventionist to control for time and attention, which enhances the scientific rigor of our trial. The interventionist provides a health education curriculum. The health education modules focus on brain health and include topics such physical activity, social engagement, sleep topics (e.g., changes in sleep that occur with aging, effects of poor sleep on health), medications/medical conditions, vision and hearing impairment. Brief telephone check-ins are comprised of review of health topics discussed during the sessions. Goals (e.g., physical activity, track medications daily) are established at the visits, and progress towards these goals is monitored in a workbook that mirrors the sleep/bladder diary of the integrated program but does not include items from the sleep/bladder diary because it is considered a self-monitoring intervention. Brief telephone check-ins (up to two) are conducted to discuss progress on goals previously established during the 5 content sessions.

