### Criteria for discontinuing or modifying allocated interventions {11b}

#### Criteria for modifying allocated interventions

The amount of sleep restriction, which is one of the components of the integrated behavioral intervention, is modified if the participant has high levels of excessive daytime sleepiness or excessive daytime sleepiness that is negatively impacting their daytime function. Stimulus control recommendations may be modified for individuals who cannot independently transfer out of bed at night. If sleepiness levels increase during the intervention, additional modifications will be made to the sleep schedule to extend time in bed. For the healthy aging education program, participants with concerns about engaging in more physical activity (e.g., due to health conditions) are not advised to increase their physical activity.

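### Adverse events are found through one general health question, so the daytime sleepiness that the plan foresees with sleep restriction may be under-counted, or counted unevenly between arms

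*Protocol article*

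**What the plan says.** All references are to the protocol article.

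- **Adverse event reporting and harms {22}.** Events are found by a single question put at every visit: "participants are asked if they have had any significant change in health status since the prior study visit". Only a yes leads to one further query, on what has changed. If an existing condition worsens, "this deterioration will be recorded as an AE even if it is related to a pre-existing condition". Events are reportable from randomization to the 4-month follow-up. Coordinators and the Site PI document them on standard forms. Nothing here differs by arm, and no directly asked symptom is listed.
- **Criteria for modifying allocated interventions.** Sleep restriction, which only the integrated program contains, is adjusted for marked daytime sleepiness. Then: "If sleepiness levels increase during the intervention, additional modifications will be made to the sleep schedule to extend time in bed". The only rule there specific to the control program concerns physical activity.
- **Criteria for discontinuing allocated interventions.** Refusing precautions about sleepiness is given as an example of why investigators may stop the program.
- **Strategies to improve adherence {11c} and Healthy aging education control arm.** Integrated-arm participants share a daily sleep/bladder diary with the interventionist. The control workbook "does not include items from the sleep/bladder diary because it is considered a self-monitoring intervention".
- **Integrated insomnia and nocturia treatment program, telephone check-ins.** The stated goal of these calls, of which there are at most two, is to check on the participant's "current sleep schedule (time in bed window), stimulus control, Freeze and Squeeze activity, and management of thoughts about sleep and voiding". Earlier material is also reviewed in light of current complaints.
- **Plans for assessment and collection of outcomes {18a}.** Blinded collection is stated for primary and secondary outcomes. Adverse events are not mentioned.

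**The concern.** The harm that the plan foresees is usually not serious. An older participant who is drowsier by day, or who dozes during an activity, need not regard this as a significant change in health. The participant sets that threshold, and a no ends the inquiry. A general question of this kind is therefore a weak instrument for the one effect that the plan expects to have to manage.

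There is also a second route by which sleepiness can come to light. To adjust a sleep schedule when sleepiness rises, someone in the integrated arm must learn that it has risen. No equivalent trigger is written for control. The article does not say whether what is learned by this route is entered on the adverse event form.

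The Data and Safety Monitor may end the trial on safety data (Interim analyses {21b}), and the abstract presents the program as aimed at "improving nocturia symptoms and overall sleep of older adults in an efficient and safe manner". Both depend on events being found well, and found alike in the two arms.

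**Working it through.** The article states no adverse event rate, detection rate or safety power, so there is no figure to reproduce. The check has two parts.

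**1. The sections side by side**

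| Element | Integrated arm | Control arm |
|---|---|---|
| General question, conditional probe, forms, reporting window | yes | yes, the same |
| Five sessions and up to two calls | yes | yes, the same |
| Written rule triggered by rising sleepiness | yes | none stated |
| Daily diary shared with the interventionist | yes, stated purpose adherence | items deliberately left out |
| Statement that sleepiness noticed in sessions goes on the form | none | none |

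The first two rows are symmetric by design. The next two could make detection differ. The last row is the gap that decides which way any error runs.

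**2. What the gap can do (illustration)**

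The only document inputs are 192 participants and 1:1 allocation, which give 96 per arm (Sample size {14}). Every rate and detection probability below is an assumption.

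Formula: observed rate = true rate × probability that an event reaches the form.

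*Branch A: only the general question feeds the form.* Assume true new sleepiness of 20% in the integrated arm (96 × 0.20 = 19.2 people) and 10% in control (96 × 0.10 = 9.6), with 25% to 50% of cases found in both arms.
- Integrated: 0.20 × 0.25 to 0.20 × 0.50 = 5% to 10%.
- Control: 0.10 × 0.25 to 0.10 × 0.50 = 2.5% to 5%.
- Observed difference: 2.5 to 5 points, against a true 10 points.

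The same branch in terms of power, with assumed true rates of 30% and 15% and 96 per arm (two-sided 5% test): the chance of a nominally significant difference is about 65% if 90% of cases are found in both arms, 45% if 60% are found, and 24% if 30% are found.

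*Branch B: interventionists' observations also feed the form.* Assume equal true rates of 20%, with 90% of cases found in the integrated arm and 60% or 30% in control.
- Integrated: 0.20 × 0.90 = 18%.
- Control: 0.20 × 0.60 = 12%, or 0.20 × 0.30 = 6%.
- Spurious difference: 6 or 12 points, nominally significant about 21% or 73% of the time with 96 per arm.
- Over true rates of 10% to 30%, the spurious difference runs from 0.10 × (0.90 − 0.60) = 3 points to 0.30 × (0.90 − 0.30) = 18 points.
- With equal detection in both arms it is zero.

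The branches are alternatives and must not be added or read as one range. They show that the direction of the error depends on a point that the article leaves open.

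**The case against.** The strongest reply is that the article says nothing false here and that formal collection is symmetric: same question, probe, forms, window and number of contacts. The eligibility criteria speak of weekly study visits, so the question may well be asked at sessions in both arms. That stands, and it rules out a stronger reading that a reader might infer, namely that sleepiness is watched only in the integrated arm and the arms' safety data are therefore not comparable. The article describes no sleepiness monitoring procedure for either arm. It does not say that control sessions omit the topic (their content includes sleep), and it gives adherence as the purpose of the diary. The assessment schedule is in a figure that is not available here.

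Two further inferences also fail. A reader might conclude that the harm goes unwatched after week 5. However, the check-in calls cover the time-in-bed window and current complaints, the reporting window runs to month 4, and sleep quality is measured in both arms after treatment and at 4 months. A reader might also treat falls as a stated risk of the program. The background ties them to nocturia and to some drugs, not to the intervention.

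It is also fair to say that the statistical sections plan no between-arm test of sleepiness, that the illustration rests on assumed rates, and that a condensed article may leave symptom lists to the full protocol. The last point limits the finding but does not remove it. The article does state a method of finding events, and that method suits the foreseen harm poorly.

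**Conclusion.** The point holds in a limited form. As written, the plan relies on a participant-judged general question to find a foreseen and usually non-serious effect, and it leaves open whether sleepiness handled through schedule changes becomes an adverse event record. Under-counting follows if it does not. Uneven counting can follow if it does and control has no equivalent route. Only one of the two can dominate.

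The size is unknown. The illustrative figures rest wholly on assumed event and detection rates and show mechanism and direction only. Non-comparable safety data are not demonstrated. The efficacy analyses are not affected. This is an inexpensive improvement that should be made. If the full protocol already contains directly asked items, it reduces to a sentence of clarification.

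**What to change.** In Adverse event reporting and harms {22}:

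1. Keep the general question. Add a short set of yes/no items, worded identically in both arms: new or worse daytime sleepiness, dozing during activity, and any fall. Falls are included because of the population, not as a presumed effect of the program.
2. Have blinded assessors ask these items at least at the post-treatment and 4-month assessments.
3. Base any between-arm safety summary on these items.
4. State that sleepiness leading to a schedule change under Criteria for modifying allocated interventions is recorded on the adverse event form. Report events found only through sessions or diary review separately.
5. If the full protocol already has such items, say so in this section and cross-refer.

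The cost is a few questions at existing contacts, a form page and a minor amendment, with slightly longer visits and higher recorded event counts in both arms. Recruitment is expected to run to June 2028, so the change can still be useful. The added items would cover only assessments made after it takes effect, and the summary should say so. No change to clinical management is proposed.

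### The 48-hour SAE rule uses a narrower relatedness test than the protocol's own criterion, so a few serious events could reach the safety monitor and the NIA later than comparable non-serious ones

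*Protocol article*

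**What the plan says.** All of the relevant text is in the protocol article, section Adverse event reporting and harms {22}. The lead-in says that SAEs go to the DSM/MSO and the NIA within time frames set by those bodies, "depending on whether events (a) are possibly related to study participation, (b) are unexpected, and/or (c) result in death or are life-threatening". It ends in a colon, and the specific rules follow:

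- Expedited SAEs: "Any SAEs that are unexpected but potentially related to the intervention will be reported to the DSM/MSO and the NIA within 48 h". The clock starts when the Site PI learns of the event.
- Remaining SAEs: "The team will report other SAEs to NIA Program Officer and to the DSM/MSO in the semi-annual AE summary", which is "provided to the DSM/MSO and the NIA, unless otherwise requested".
- Expedited non-serious events: "Non-serious AEs that are considered to be UPs, by virtue of being unexpected but possibly related to study participation". These go to the same two bodies in 5 working days, counted from when the Principal Investigators learn of them.
- Remaining non-serious events: the semi-annual summary.

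The same section sets a separate route to the ethics board: "written notification of the IRB within 5 business days after becoming aware of any local SAE that is both unanticipated and related to the research". Events are reportable from randomization to the 4-month follow-up.

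**The concern.** The lead-in and the non-serious rule both judge relatedness against study participation. Only the 48-hour SAE rule judges it against the intervention. Study participation is the wider base: it takes in follow-up assessments and the conditions placed on participants as well as the programs. Because the rule for remaining SAEs catches everything that the 48-hour rule leaves out, the narrower wording moves a class of unexpected, possibly related serious events to the slowest channel, while their non-serious counterparts stay on a short clock.

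What is at stake is how soon the safety monitor and the funder hear of such an event. Both have a say in whether the trial continues: the NIA under Role of sponsor {5c}, and the DSM/MSO under Interim analyses {21b}.

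**Working it through.** The protocol states no figure to reproduce. The check is to trace each class of unexpected event through the rules for the DSM/MSO and the NIA.

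**Step 1: relatedness test in each sentence**

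- Lead-in for SAEs: "are possibly related to study participation".
- 48-hour SAE rule: potentially related to the intervention.
- Rule for remaining SAEs: no test of its own; it takes whatever the 48-hour rule leaves.
- Non-serious rule: possibly related to study participation.

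**Step 2: resulting clocks for an unexpected event**

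| Possibly related to | Serious | Non-serious |
|---|---|---|
| an allocated program | 48 h | 5 working days |
| study participation, but neither program | semi-annual summary, unless otherwise requested | 5 working days |

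The first row is ordered as one would expect. In the second row the serious event has the longer clock. With two summaries a year, the longest wait is 12 / 2 = about 6 months, assuming even spacing. That is an outer bound, not an expected delay.

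**Step 3: could another rule catch the second-row SAE?**

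- The 5-working-day rule is confined to non-serious events, so it does not.
- The IRB route uses relation to the research, which is wide enough to include study procedures. It covers local SAEs, omits the qualifier *possibly*, and goes to the IRB rather than to the DSM/MSO or the NIA.
- The exception for requests, and the reference to time frames set by the DSM/MSO and the NIA, allow a shorter clock, but none is stated.

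**Step 4: is the class empty?** It is small but not empty.

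- The blood and urine tests, bladder scan and home sleep apnea test described under Recruitment {15} belong to the assessment before randomization, so they fall outside the reportable window.
- After randomization, assessments take place 1 week after the intervention and at 4 months (Statistical methods {20a}, Aim 1). The outcomes listed under Outcomes {12} are questionnaires and a 7-day diary, which carry little risk.
- Participants are also advised not to start new bladder or sleep medications, or outside behavioral treatment, during the trial (Relevant concomitant care {11d}). An SAE attributed to that condition would relate to participation but to neither program.
- The timeline figure is not available, so other follow-up procedures can be neither confirmed nor excluded.

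**The case against.** The best defense is that this is loose wording and not a decision to delay anything. The lead-in states the wider criterion and introduces the rules directly, so the intervention may be shorthand in a condensed article. The DSM/MSO and the NIA can set or request shorter times, and coordinators must bring a possible SAE or unanticipated problem to the Site PI more urgently. The follow-up documented in the article is low risk, and the interim analysis section calls the interventions minimal risk. All of this stands as to how rarely the gap would matter. It does not remove the mismatch: the rules are set out as a closed set with a residual clause, they disagree with their own lead-in, and no safeguard states a shorter clock to the two bodies concerned.

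A reader might also infer that the intervention means the integrated program alone, so that SAEs linked to health education would be reported late and harms compared unevenly between arms. The document does not support that:

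- The safety section has the Site PI judge the relationship to study interventions, in the plural.
- Criteria for modifying allocated interventions {11b}, Strategies to improve adherence {11c}, Sample size {14} and Who will be blinded {17a} all use the word for both programs. The contrast between intervention and control groups in Statistical methods {20a} labels the analysis groups.
- Events are elicited at each study visit and recorded on standardized forms, with no distinction by arm, and every SAE reaches the monitor eventually. The wording affects the speed of individual reports, not what is collected or compared.

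**Conclusion.** The concern holds in a limited form. The 48-hour SAE rule is narrower than the criterion it is meant to implement and narrower than the rule for non-serious events. For an unexpected SAE related to study participation but to neither program, the text gives a wait of up to about 6 months to the DSM/MSO and the NIA, against 5 working days for the non-serious equivalent and 48 hours for a program-related SAE.

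This rests on three assumptions: the rules are applied as written, no shorter time has been requested, and the two yearly summaries are evenly spaced. The protocol gives no number of such events, and they are probably rare. The natural reading of the intervention in the safety section covers both programs, so no asymmetry between arms is claimed. The severity is minor: an inconsistency in safety reporting that does not touch the design, sample size or analysis.

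**What to change.** Reconcile the relatedness wording within the adverse event section. In the 48-hour SAE rule, replace relation to the intervention with the protocol's own criterion (a), possible relation to study participation, and add that this covers both programs and any study procedure. The SAE rule would then match its lead-in and the non-serious rule, and the added clause would settle the meaning for the control program. Make the same change in the safety monitoring plan if it repeats the phrase.

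The cost is one phrase, submitted as a protocol modification, and at most a few more 48-hour reports. Recruitment is expected to run to June 2028, so the change would still apply to participants yet to be enrolled.
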